#### Secondary Outcomes

We used several measures of social connectedness. The Interpersonal Needs Questionnaire describes the extent to which individuals feel connected to others (ie, belongingness) and the extent to which they perceive themselves to be a burden on other people (ie, burdensomeness) [23,26]. Previous psychometric analyses indicated that the latent variable “thwarted belongingness” significantly predicted suicidal ideation scores, supporting the measure’s construct validity [9]. The Loneliness Scale, which is part of the National Institutes of Health Toolbox Social Relationship Scales [27], assesses feelings of loneliness and exhibits both internal reliability and concurrent validity. The Social Distress Scale, also part of the National Institutes of Health Toolbox, measures perceived rejection and hostility and has good internal reliability and concurrent validity [27]. The Social Contact Questionnaire asks participants about their use of various forms of social contact, such as text messaging, email, and postal mail [28]. Finally, the Social Connection Measure asks participants to choose which of 7 Venn diagrams, each with a progressively greater proportion of overlap, best reflects their sense of closeness to their community [29]. This measure is intended to provide participants with a means of visualizing their integration within their community.

#### Covariates and Other Measures of Interest

Participants were also asked to complete surveys related to several other aspects of mental health so that they could later be assessed as possible mediators or effect measure modifiers. The Acquired Capability for Suicide Scale is a 20-item measure that quantifies one’s fearlessness about and capability to die by suicide [30-32]. It has adequate to good internal consistency (α=–.67 to .83), convergent and discriminant validity, and does not correlate with measures of depression or suicidal ideation. The Exposure to Suicide Questionnaire asks about participants’ exposure to suicide and suicide attempts made by family members, friends, or coworkers to assess possible contagion effects. This information allows a posthoc examination of the impact of exposure to suicide and suicide clusters on the intervention effects.

The Breslau Post Traumatic Stress Disorder Screening is a 7-item scale that assesses internalization of feelings following an upsetting or frightening event [33]. Questions about feelings in the past month are answered yes or no and summed to create a total score ranging from 0 to 7; higher scores indicate probable posttraumatic stress disorder. The Ayers Coping Scale is an 8-item scale that has been validated among AIAN populations to assess the frequency of using healthy coping strategies when faced with a problem [34]. The Kessler Psychological Distress Scale, also validated for administration to AIANs, is a 6-item scale that assesses the frequency of feelings of anxiety, hopelessness, depression, restlessness, and unworthiness in the past 30 days [35]. The scale is sensitive (0.36, 0.08) and specific (0.96, 0.02) with respect to predicting serious mental illness [35].

The Historical Loss and Trauma Scale is a 12-item self-report measure that assesses the frequency of thoughts regarding historical trauma (eg, “how often do you think about the loss of our traditional spiritual ways” and “how often do you think about the loss of our language”), which has high internal reliability [36-38]. The Oetting and Beauvais Orthogonal Ethnic Identification Scale poses 8 questions regarding the degree to which respondents follow the tribal and white way of life and the importance of keeping their tribal identity, values, and practices [39,40].

The EuroQol 5-Dimension 5-Level (EQ-5D-5L) is a 6-item measure that assesses respondents’ capacity to perform activities related to mobility, self-care, usual activities, and health dimensions, including pain, discomfort, anxiety, and depression, as well as overall self-reported health status [41,42]. The Health Economics Analysis Questionnaire estimates use of outpatient, inpatient, and emergency room visits; out-of-pocket costs of care; health insurance; employment and schooling benefits; income; publicly funded benefits; lifestyle behaviors (eg, substance use); and costs of participating in the study.

Self-reported drug use and drug use severity are assessed using the Addiction Severity Index, Native American Version [43]. This is a comprehensive measure of lifetime and current drug and alcohol use, as well as the impact of substance abuse on medical conditions, psychiatric well-being, employment status, and encounters with the legal system. The culturally adapted version of the measure also addresses the impact of substance use on the respondent’s ability to participate in cultural or traditional activities and ceremonies.

Demographic information included gender, sexuality, relationship status, religion, number of children, living arrangement, employment, use of the native language, and education level. Demographic features that may change are reassessed at 12 months.

The COVID-19 Impact on Well-Being Survey, a brief 5-item survey, assesses the impact of COVID-19 infection, the pandemic, and related mitigation efforts on participants’ economic, social, and overall health well-being.

We also queried intervention participants at follow-up about their experience of and satisfaction with caring texts.

#### Treatment Retention

Retention in the SBIRT program is assessed at 12 months. It is operationalized as a 3-category indicator (full, partial, and none) defining engagement for each participant in the appropriate level of care. The appropriate level of care is determined during the initial in-person session with the SBIRT behavioral therapist before enrollment in the study and is independent of study procedures. These variables will be included in sensitivity analyses if they appear unbalanced, although randomization and the large sample size should balance the severity of suicidality and intensity of appropriate intervention services across the study conditions.

### Data Analysis

#### Analysis plan

We expect that individuals receiving the culturally tailored text messages will have better outcomes than those in the treatment-as-usual control arm. Chi-square and *t* tests will be used to compare the overall percentages (binary outcomes) and mean differences (continuous outcomes) between study arms. We will conduct a sensitivity analysis using logistic or linear regression to adjust for baseline factors that are imbalanced between the intervention and control arms. Results will be presented as risk ratios and risk differences for binary outcomes, extracted from logistic regression models using marginal standardization, with 95% CIs [44,45]. Primary analyses will use an intention-to-treat approach.

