**Methods:**

This 2-arm, double-blinded, randomized controlled trial is being implemented at 2 clinical sites with large AI populations. Partnering with clinics in Albuquerque, New Mexico, and Rapid City, South Dakota, we are recruiting AI adults aged 18-34 years to participate in a caring text message study. During the baseline visit, participants complete several surveys and an interview with study staff to understand their history of suicidal behavior. After completion of the baseline visit, participants are randomized to receive the intervention—approximately 30 caring text messages—or treatment as usual. The text messaging platform selected for this study allows bidirectional messaging; while there is no expectation that participants respond, they can provide feedback or seek additional resources. Participants are followed up at 6 and 12 months postbaseline. At the final 12-month follow-up visit, they complete many of the same surveys and participate in an interview to ascertain suicidality since their initial visit. The primary outcomes of interest are suicide-related behaviors—suicidal ideation, suicide planning, suicide attempt, or thoughts and actions requiring hospitalization. Secondary outcomes include social connectedness and other measures of mental health. We will use an intention-to-treat analysis with logistic and linear regression to calculate odds ratios and risk differences (95% CIs) for binary and continuous outcomes.

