#### Randomization

Randomization to the intervention group or the treatment-as-usual (TAU) control group occurred after the baseline assessment had been completed. A biostatistician not involved with data collection programmed the randomization module in REDCap to enable site coordinators to access the assignment for each participant in real time. Randomization was stratified by site. To prevent bias that might arise when study coordinators intentionally or unintentionally anticipate an upcoming randomization assignment, assignments were blocked in randomly patterned groups of 2, 4, or 6, with assignments for each arm distributed evenly within each block. Follow-up interviews for the SASI were completed by staff blinded to the participants’ treatment allocation.

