#### Primary Outcomes

Our primary outcome of interest was suicidal behavior. While suicidal ideation is more common than suicide attempts or attempts requiring hospitalization, ideation is not necessarily a concrete event and can be more difficult to measure. For this reason, ideation, attempts, and suicide-related hospitalization were all selected to measure the same underlying risk construct. The Suicidal Ideation Questionnaire-Junior, which has been validated with AIAN individuals, measured the study’s primary outcome of suicidal ideation [22]. It consists of 15 items that evaluate thoughts of death, desire to be dead, and specific thoughts of self-harm. Scores range from 0 to 90, with scores above 32 indicating active suicidal ideation [23]. The “junior” version of the questionnaire was used to accommodate participants with lower reading levels.

The SASI count (lifetime and recent) assessed the primary outcome of suicide attempts [24]. It is a concise questionnaire that determines the first, most recent, and most severe suicide attempt or nonsuicidal self-injury. It assessed the date, method used, and intent to die (ie, clear intent to die, ambivalent intent, or no intent to die), the highest level of medical treatment received (ie, none, doctor or clinic visit, emergency room, or admission to a medical unit), and lethality of each event. The SASI also posed questions about the number of attempts for each of the 17 methods, specifying intent to die, medical treatment received, and lethality for each one. Intent to die and lethality were derived from the SASI interview [24]. A lifetime version of the instrument administered at the baseline assessment captured all historical suicide attempts or nonsuicidal self-injury. A recent version of the instrument assessed only those events that occurred in the past year, both at baseline and follow-up assessments. The adapted version of the SASI used in this study simplified the language, included methods commonly used in AIAN communities, and added an assessment of drug and alcohol use at the time of the self-injury. The SASI was administered via interview.

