#### Power and Sample Size

We plan to recruit 350 people across both sites. We assume the study will have 70% retention at 12 months, yielding an analytic sample of 240 people (120 per group). With this sample, we will have 80% power to detect a 16% difference (Risk Ratio=0.47) in suicidal ideation between intervention and TAU groups, assuming that 30% of the TAU group reports suicidal ideation at follow-up. We will also be able to detect an 11% difference (Risk Ratio=0.25) in suicide attempts if 15% of the TAU group participants attempt suicide within the 12-month follow-up. There is variability in the literature regarding what constitutes a clinically meaningful effect size for reductions in suicidality and the best means of measuring such an effect (eg, degree of suicidality, reported number of attempts, etc). Regardless, we are confident in our ability to recruit a sizeable analytic sample in a difficult-to-reach population.

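### Arms are compared unadjusted, the adjusted analysis picks covariates by observed imbalance, site and baseline outcome values go unused, and the Abstract states a different analysis

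*Protocol article*

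**What the plan says.** **Protocol article, Analysis plan.** Chi-square and t "tests will be used to compare the overall percentages (binary outcomes) and mean differences (continuous outcomes) between study arms". Adjustment appears only in a "sensitivity analysis using logistic or linear regression to adjust for baseline factors that are imbalanced between the intervention and control arms". The section then says "Results will be presented as risk ratios and risk differences for binary outcomes", "extracted from logistic regression models using marginal standardization, with 95% CIs", without naming any covariate in those models.

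**Treatment Retention.** The same rule returns: level-of-care variables enter sensitivity analyses only if they look unbalanced.

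**Randomization.** "Randomization was stratified by site". No analysis section mentions site.

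**Primary Outcomes.** The past-year version of the SASI is given at both baseline and follow-up. Baseline collection of the SIQ-Junior is implied by the Abstract's account of repeated surveys, but is not stated outright. No analysis section names a baseline value as a covariate.

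**Abstract, Methods.** The intention-to-treat analysis is "logistic and linear regression to calculate odds ratios and risk differences (95% CIs) for binary and continuous outcomes".

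**The concern.** Three things sit badly together.

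1. The design balances the arms on site and records the past-year value of at least one primary outcome at baseline, yet the arm comparison uses neither. The likely cost is wider intervals than the data allow, in a trial powered only for large effects (risk ratios 0.47 and 0.25).
2. Choosing covariates by observed imbalance is a poor rule. Under randomization an imbalance is chance. The rule can admit factors that do not predict outcome and leave out strong predictors that happen to balance, and it leaves the meaning of imbalanced to the analyst.
3. The Abstract and the Analysis plan name different analyses and different ratio measures (odds ratio v risk ratio). The Analysis plan is also unclear in itself. Marginal standardization of a logistic model containing arm alone returns the crude proportions, so the step adds nothing unless the model has covariates, and none is named.

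**Working it through.** **Inputs from the document:** 120 per arm analysed; 80% power; ideation 30% under treatment as usual with a 16-point difference; attempts 15% with risk ratio 0.25; 1:1 allocation; two sites.

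**Assumed, because not stated:** two-sided alpha 0.05; baseline-outcome correlation 0.3-0.7; baseline log odds ratio 0.7-1.8 per SD; equal-sized sites with the rates shown below.

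**Step 1. Reproduce the stated power.** For two proportions with pooled variance:

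n0 = [1.96 √(2p̄(1−p̄)) + 0.8416 √(p1(1−p1) + p2(1−p2))]² / (p1−p2)²

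Continuity correction: n = (n0/4)[1 + √(1 + 4/(n0(p1−p2)))]²

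- Ideation, 0.30 v 0.14, p̄ = 0.22: n0 = (1.148 + 0.484)²/0.0256 ≈ 104.0 (105 per arm). Corrected, 117 per arm. Corrected power at 120 is 81.4%; uncorrected, 85.4%.
- Attempts, 0.15 v 0.15 × 0.25 = 0.0375: corrected, 122 per arm; power at 120 is 79.5%.

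Both agree with 120 per arm and 80%. The stated power is therefore that of an unadjusted two-proportion test, with no site or baseline term.

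**Step 2. Baseline adjustment, continuous outcome.** The effect that gives the t test 80% power is (1.96 + 0.8416)√(2/120) = 0.362 SD. Adjusting for a baseline score with correlation ρ multiplies the residual SD by √(1−ρ²), so power = Φ(2.8016/√(1−ρ²) − 1.96).

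| ρ | Power, prespecified adjustment | Detectable effect (SD) | Equivalent unadjusted n per arm, 120/(1−ρ²) |
|---|---|---|---|
| 0.3 | 83.6% | 0.345 | 132 |
| 0.5 | 89.9% | 0.313 | 160 |
| 0.7 | 97.5% | 0.258 | 235 |

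**Step 3. The imbalance rule, if it decided the analysis.** In 20,000 simulated trials per setting, the baseline score was adjusted for only when it differed significantly between arms. Power was 80.1%, 80.8% and 81.4% at ρ = 0.3, 0.5 and 0.7, and type I error was 4.6%, 4.4% and 3.5%. Nearly all of the gain in Step 2 is lost.

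**Step 4. Baseline adjustment, ideation at 30% v 14%.** 3,000 simulated trials per setting, uncorrected chi-square v logistic regression with one baseline score:

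| Log odds ratio per SD | Chi-square | Adjusted logistic |
|---|---|---|
| 0.7 | 86.2% | 88.2% |
| 1.2 | 86.9% | 91.7% |
| 1.8 | 85.8% | 95.0% |

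The starting point is above 80% because this chi-square has no continuity correction (compare 85.4% in Step 1).

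**Step 5. Site term alone.** 200,000 simulated trials per setting, 60 per arm per site:

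| Site rates | Size, chi-square | Size, stratified | Power, chi-square | Power, stratified |
|---|---|---|---|---|
| 30/30% | 5.0% | 5.1% | 86.1% | 86.1% |
| 25/35% | 4.8% | 5.0% | 86.1% | 86.3% |
| 20/40% | 4.5% | 5.1% | 86.5% | 87.1% |
| 15/45% | 3.8% | 5.2% | 87.0% | 88.5% |

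The largest gain is 88.5 − 87.0 = 1.5 points. Ignoring site makes the test conservative, not liberal.

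**Step 6. How many terms the attempts model can carry.** Expected attempters: 120 × 0.15 + 120 × 0.0375 = 18 + 4.5 = 22.5. Arm, site and one baseline term give 22.5/3 = 7.5 events per term; a fourth term gives 22.5/4 ≈ 5.6.

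**The case against.** The strongest reply is that this is a matter of efficiency and not an error. Unadjusted chi-square and t tests are valid in a 1:1 randomized trial, and Step 1 shows that the sample size was built for them. That stands. A reader might infer bias, inflated type I error or an undermined sample size; Steps 1 and 5 support none of these.

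The imbalance rule is confined to sensitivity analyses. If the raw tests are the primary analysis, the rule cannot move the primary result. That also stands, with one qualification: the text does not say whether the logistic models behind the reported risk ratios carry those covariates. Nor does it label the raw tests primary; that follows only from calling the adjusted regression a sensitivity analysis.

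A full covariate list is commonly left to a statistical analysis plan that is not shown. That is fair, and its absence is not the point. The article does state a selection rule, and it states two different analyses.

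A reader might also infer that the 0-90 SIQ-Junior score will be analysed only as yes or no, because the Power section works from a proportion ("assuming that 30% of the TAU group reports suicidal ideation at follow-up") and the measure has a cut-off ("Scores range from 0 to 90, with scores above 32 indicating active suicidal ideation"). The document does not say so. Its Analysis plan provides t tests for continuous outcomes and its Abstract provides linear regression. No gain from a change of outcome scale is claimed here.

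Finally, adjustment is not free for rare outcomes. With about 22 attempts expected, a model with many terms risks small-sample bias or separation. This stands and limits the fix.

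**Conclusion.** The point holds as one of lost precision, an unsound covariate rule and inconsistent statements of the analysis. The plan's comparison is valid but leaves available information unused. The gain from prespecified baseline adjustment is about 4 to 17 points of power for continuous outcomes (80% to 84-97%) and about 2 to 9 points for ideation at the planned rates. These ranges rest on assumed correlations and log odds ratios, since the document gives none. They also need a baseline value of the outcome, which is explicit for the SASI and only implied for the SIQ-Junior. The site part is minor, at most about 1.5 points even with site rates of 15% and 45%. The difference between the Abstract and the Analysis plan needs no assumption and must be reconciled in any case.

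**What to change.** - State one primary model per outcome, with arm, site and the baseline value of that outcome where collected. Use linear regression for continuous outcomes. For binary outcomes use logistic regression, reporting the marginally standardized risk difference and risk ratio that the Analysis plan already intends.
- For sparse outcomes such as attempts, limit covariates to site and one baseline term, or use a penalized or site-stratified method.
- Delete observed imbalance as the rule for choosing covariates, in both the Analysis plan and Treatment Retention.
- Keep the chi-square and t tests as supportive.
- Align the Abstract's analysis and effect measure with the Analysis plan.
- Confirm that the SIQ-Junior was collected at baseline.

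The cost is a change of wording, made before outcomes are compared by arm. It needs no new visits and no larger sample. The small downside is that models for rare outcomes must be kept sparse.

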#### Missing Data

Our primary analysis will rely on complete case analysis. We will conduct sensitivity analyses with multiple imputation methods. Multiple imputation through chained equations will be applied when data are missing at random. We will also conduct sensitivity analyses to exclude individuals who were randomized to receive the intervention but did not receive it per the schedule outlined in Table 2 due to technological errors or temporary lapses in access to cell phone service. These additional sensitivity analyses will improve confidence in our findings.

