#### Caring Texts Intervention

In addition to receiving TAU, participants assigned to the caring texts intervention group also received 28-30 supportive and nondemanding text messages; examples of these messages are available in Table 1, and the complete schedule of messages is available in Multimedia Appendix 1. The number of messages sent depended on the date of enrollment, the participant’s birthday, anniversaries, holidays, and seasonal and local events. These messages were sent over 12 months, namely, daily for the first 3 days, then 6 weekly messages, 6 biweekly messages, and 6-monthly messages. Other messages include a birthday message, a holiday message (in December), a harvest message (in November), messages acknowledging an anniversary of loss and an anniversary of hope, and 4 messages for seasonal events. The study tailored messages to reflect locally appropriate holidays, events, and celebrations, and used the local language for greetings [20]. The messages were delivered through a secure online platform, LifeWIRE (LifeWIRE Group), which was compliant with HIPAA, HiTech, and FDA regulations for electronic interactions. This platform tracked all communication, preprogrammed messages, and offered the option for individualized responses to be typed and stored for record-keeping purposes.

**Table 1 table1:** Sample messages for caring text messages sent to intervention participants by site.

Timing	FNCH^a^ message (Albuquerque)	OHC^b^ message (Rapid City)
First day after enrollment (#1)	It was nice meeting and talking with you yesterday, [displayname]^c^. You showed great courage. Thanks for trusting me. -<staff name>^d^	Hello [displayname], It was nice meeting and talking with you yesterday. You showed great courage. Thanks for trusting me. -<staff name>
Weekly (#6)	Ya’at’eeh! Keshi! Guw’aadzi! No matter how you say “hello,” everyone is welcome at the FNCH Traditional Wellness Program. Please call (XXX) XXX-XXXX for more information. - <staff name>	Aŋpétu wašté [displayname]! Sending you positive vibes. Creator has good things for you. Smudging is a good way to stay in touch with the Creator. - <staff name>

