### Measures

A summary of all measures used in the study is available in Table 2. Unless otherwise noted, measures were administered as a survey in REDCap.

**Table 2 table2:** Summary of outcome and measures used in the urban caring text study.

Type, topic, and domain			Scale or measure

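### The delivery sensitivity analysis excludes people after randomization from the intervention arm only, so it can be biased in either direction, and its criterion cites a table with no message schedule

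*Protocol article*

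**What the plan says.** The Analysis plan section states: "Primary analyses will use an intention-to-treat approach". The Missing Data section adds: "Our primary analysis will rely on complete case analysis", with multiple imputation as a sensitivity analysis. It then announces a further sensitivity analysis that will "exclude individuals who were randomized to receive the intervention but did not receive it per the schedule outlined in Table 2", when the failure was "due to technological errors or temporary lapses in access to cell phone service". No matching exclusion is stated for the TAU arm. The paragraph closes: "These additional sensitivity analyses will improve confidence in our findings".

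Table 2, in the Measures section, is captioned "Summary of outcome and measures used in the urban caring text study" and lists outcomes and covariates. The Caring Texts Intervention section describes the message timing in prose and says that "the complete schedule of messages is available in Multimedia Appendix 1". On the delivery platform, the same section says: "This platform tracked all communication".

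**The concern.** Whether a participant received the messages on schedule is known only after randomization, and the exclusion can apply only to those assigned to texts. Phone trouble is not confined to that arm. Every participant must have a phone at entry (Eligibility), and the Recruitment and Retention section foresees, without naming an arm, that some will lose the ability to text. TAU participants with the same lapses stay in, so a selected text group is compared with an unselected control group.

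The exclusion cannot simply be mirrored in TAU. That arm receives only contact-check and appointment messages, so there is no comparable delivery record.

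If the people removed differ in suicide risk from those kept, the contrast moves away from the treatment effect. What is at stake is a possibly biased as-delivered estimate being read as support for the primary result. Separately, the exclusion criterion relies on a schedule that is not in the table it cites.

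**Working it through.** **Inputs.** From Power and Sample Size: 30% ideation in TAU, 120 analysed per arm, a 16-point detectable difference and 80% power. Assumptions, because the article gives no figures: the share *f* of the intervention arm removed, the risk of those removed, and two-sided alpha 0.05.

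**The plan's own figure.** 30% minus 16 points is 14%, and 14/30 = 0.47, the stated risk ratio. With 120 per arm, the continuity-corrected two-proportion test has 81.4% power, in line with the stated 80%. This point disputes no planning figure; 30% and 120 serve only as inputs.

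**Bias with no true effect.** Both arms have overall risk *p* = 0.30. If those removed have risk *q*, the retained risk is (*p* − *f q*)/(1 − *f*). If their risk is *k* times that of the rest, it is *p*/(1 − *f* + *f k*). The comparison is with the whole TAU arm at 0.30.

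| Share removed | Risk of those removed | Retained risk | RR | RD (points) |
|---|---|---|---|---|
| 20% | 45% | (0.30 − 0.09)/0.8 = 0.2625 | 0.875 | −3.75 |
| 20% | 30% | (0.30 − 0.06)/0.8 = 0.30 | 1.00 | 0 |
| 20% | 0.67 × rest | 0.30/0.934 = 0.321 | 1.07 | +2.1 |
| 20% | 2 × rest | 0.30/1.2 = 0.25 | 0.83 | −5.0 |
| 10% | 45% | (0.30 − 0.045)/0.9 = 0.283 | 0.94 | −1.7 |
| 30% | 45% | (0.30 − 0.135)/0.7 = 0.236 | 0.79 | −6.4 |

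Holding the removed group's risk at 45% does not hold its relative risk constant. Against the rest it is 0.45/0.283 = 1.59, 0.45/0.2625 = 1.71 and 0.45/0.236 = 1.91 for 10%, 20% and 30% removed.

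**Against sampling error.** With 20% removed, 96 are compared with 120. In the 45% case the standard error of the difference is √(0.30×0.70/120 + 0.2625×0.7375/96) = 0.061. The bias of 0.0375 is about 0.6 standard errors, and 3.75/16 = 23% of the design difference. With 20% removed at twice the risk of the rest, the chance of a significant result favouring the texts is 12.4%, against a nominal 2.5%. At equal risk it stays at 2.5%; at 0.67 times the risk it falls to 1.1%.

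**An estimate that keeps both arms.** TAU participants cannot receive the intervention messages, so the complier-average risk difference is the intention-to-treat difference divided by the share of the text arm that received them. With no effect and 80% receipt this is 0/0.80 = 0, whatever the risk of the non-receivers. Its standard error is roughly 1/0.80 = 1.25 times that of the intention-to-treat difference.

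**The reference.** Table 2 contains only measures, and Table 1 contains sample messages. The prose schedule gives 3 + 6 + 6 + 6 = 21 timed messages plus 1 birthday, 1 holiday, 1 harvest, 2 anniversary and 4 seasonal messages. That makes 30, consistent with the stated 28-30. The intended schedule is therefore that prose and Multimedia Appendix 1.

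**The case against.** A reader might infer that the exclusion favours the texts as a matter of course, because loss of phone service suggests instability and higher risk. The article does not support that. It reports nothing on the risk of people whose messages failed. One of its two reasons, technical error, lies with the system and may be unrelated to risk. The other concerns lapses that it calls temporary. Depending on the assumption, the bias is downward, absent or upward.

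Three further objections have weight:

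- The primary analysis is intention-to-treat, and the exclusion is labelled a sensitivity analysis. Nothing says it would override the main result. The closing claim about confidence covers several analyses, multiple imputation among them.
- Outcomes are analysed on complete cases. People with lasting loss of contact would tend to miss follow-up in either arm, so the one-sided removal concerns only those with delivery failures who still gave a 12-month outcome. The relevant share may be smaller than the share with any lapse.
- The table citation is a wrong number with a recoverable target. A precise receipt threshold may stand in an analysis plan not shown here, so its absence from the article is not held against the plan.

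These points limit the size and consequence. They do not restore the balance that randomization gave, and no other section of the article repairs the one-arm rule.

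**Conclusion.** The point holds in conditional form. The contrast is not protected by randomization and can be biased: towards the texts if those removed are at higher risk, not at all if removal is unrelated to risk, and against the texts if they are at lower risk. With 20% removed and no true effect, the illustrations run from RR 0.83 to 1.07. Both the share and the risks are assumptions, so this is a range of possibilities and not an estimate of what will happen.

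It would go too far to conclude that the trial's main result is compromised; the primary analysis does not use the exclusion. The issue is minor to moderate. The claim that such analyses improve confidence cannot be made for this one, since agreement with the primary result could come from selection. The reference to Table 2 is wrong.

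**What to change.** Replace the exclusion with a complier-average (instrumental-variable) estimate, or keep the exclusion beside it with the complier-average estimate as the main as-delivered result. Use assignment as the instrument, keep participants of both arms as randomized, and handle missing outcomes as in the primary and multiple-imputation analyses.

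Define receipt from the platform records before unblinding, either as any message delivered or as the proportion of scheduled messages delivered. A cut-off that counts partial receipt as none should be avoided: if the few messages received have an effect, the exclusion restriction fails and the estimate is inflated. State that assumption, namely that assignment affects outcomes only through the messages. If the proportion is used, also state that the effect is taken as linear in the share delivered.

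If the exclusion analysis is kept, label it per-protocol and not protected by randomization, and drop the confidence claim for it. Point the criterion to the Caring Texts Intervention section and Multimedia Appendix 1 instead of Table 2.

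The cost is a few lines of analysis plan and no new data collection. The downsides are a wider confidence interval, an added assumption that cannot be fully tested, and reliance on how well the platform records capture delivery. The article says communication was tracked, but not that receipt on the handset was recorded during a service lapse.
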